#### Exclusion criteria

Participants will be excluded if they meet any of the following conditions:

prior receipt of surgery, chemotherapy, radiotherapy, immunotherapy, or targeted therapy for cervical cancer;non-epithelial cervical malignancies or rare histological subtypes such as neuroendocrine carcinoma, small cell carcinoma, clear cell carcinoma, or sarcoma;known distant metastases at the time of enrollment confirmed by imaging studies;contraindications to radiotherapy (such as prior pelvic radiation, active inflammatory bowel disease, or connective tissue disorders affecting the pelvis) or chemotherapy (such as severe hypersensitivity to platinum compounds);history of other malignancies within the past 5 years, except for adequately treated basal cell or squamous cell carcinoma of the skin, carcinoma *in situ* of the cervix, or carcinoma *in situ* of the breast;pregnancy confirmed by serum or urine β-human chorionic gonadotropin test, or lactation;severe psychiatric disorders or cognitive impairments that would impair the ability to understand the study requirements or provide informed consent;active, uncontrolled infections requiring systemic antibiotic, antifungal, or antiviral therapy;significant cardiovascular disease including New York Heart Association class III or IV heart failure, unstable angina, myocardial infarction within 6 months, or serious cardiac arrhythmias;participation in other interventional clinical trials during the study period that could potentially interfere with study assessments or outcomes.

#### Withdrawal criteria

Participants may be withdrawn from the study under the following circumstances:

voluntary withdrawal of informed consent for any reason at any time without prejudice to future medical care;inability to complete the planned treatment regimen due to unacceptable toxicity or deteriorating performance status;inability to comply with the follow-up schedule or protocol requirements as judged by the investigator;occurrence of severe adverse events (SAEs) requiring permanent discontinuation of CCRT, such as grade 4 hematologic toxicity, grade 3–4 non-hematologic toxicity not manageable with supportive care, or life-threatening complications;major protocol violations that compromise data integrity or patient safety, such as failure to obtain required blood samples at critical time points or deviation from prescribed treatment regimens;development of disease progression requiring change in treatment approach during the planned CCRT course;investigator’s judgment that continued participation is not in the patient’s best interest based on medical, safety, or ethical considerations.

Data collected from withdrawn participants up to the point of withdrawal will be included in the analysis according to the intention-to-treat principle unless consent for data use is specifically withdrawn.

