**Figure 1 f1:**
[figure not shown]
Study flow diagram.

Eligible participants will be consecutively recruited from patients diagnosed with HPV-associated cervical cancer at our institution. Study-related examinations and blood sampling will be performed according to the protocol schedule outlined in **Table 1**. Importantly, this study does not involve investigational drugs or experimental interventions. All patients will receive standard-of-care CCRT according to National Comprehensive Cancer Network (NCCN) guidelines and Chinese Society of Clinical Oncology (CSCO) recommendations. No study medications will be provided free of charge, and no financial compensation or additional economic incentives will be offered to participants, treating physicians, or research staff for trial participation.

**Table 1 T1:** Schedule of enrolment, interventions, and assessments.

Study period	Enrolment	Allocation	Treatment & monitoring			Post-treatment follow-up		
Procedure/assessment	Screening (-t_1_)	Baseline (T0)	Week 3-4 (T1)	End CCRT (T2)	3 months (T3)	6 months	12 months	18–24 months
Enrolment								
Eligibility screening	X							
Informed consent	X							
Allocation		X						
Medical history	X							
Assessments								
Demographics/baseline	X	X						
Physical examination	X	X	X	X	X	X	X	X
ECOG performance status	X	X	X	X	X	X	X	X
Vital signs (BP HR T)	X	X	X	X	X	X	X	X
Concomitant medications	X	X	X	X	X	X	X	X
Laboratory tests	X	X		X	X	X	X	X
HPV DNA testing (cervical)	X							
Imaging								
Pelvic MRI	X	X			X	X	X	X
PET-CT (if indicated)	X				X	X	X	X
Treatment								
CCRT administration		X	X	X				
Treatment adherence		X	X	X				
Blood sampling								
Plasma HPV ctDNA		X	X	X	X	X	X	X
ctDNA analysis								
ddPCR (all samples)		X	X	X	X	X	X	X
NGS (subset)		X		X	X			
Response assessment								
RECIST 1.1 evaluation					X	X	X	X
Safety & qol								
Adverse event monitoring		X	X	X	X	X	X	X
EORTC QLQ-C30/CX24		X		X	X	X	X	X
Data management								
CRF completion	X	X	X	X	X	X	X	X
Data verification					X		X	X
Query resolution	Ongoing throughout study period							

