### Blood sampling and time points for ctDNA detection

Peripheral venous blood samples (10 milliliters [mL] per time point) will be collected into ethylenediaminetetraacetic acid (EDTA)-anticoagulated tubes (Becton Dickinson, Franklin Lakes, New Jersey, USA) at the following predefined time points to capture ctDNA dynamics throughout the treatment course and follow-up period:

T0 (baseline): Within 7 days before initiation of CCRT. This baseline sample will establish the pretreatment HPV ctDNA level as a reference point and will be correlated with baseline tumor burden assessed by imaging and clinical examination.

T1 (mid-treatment): After 3–4 weeks of CCRT (approximately 15–20 fractions of radiotherapy and 3–4 cycles of concurrent chemotherapy).

T2 (end of CCRT): Within 1 week after completion of all CCRT including brachytherapy.

T3 (first evaluation): At 3 months (± 2 weeks) after completion of CCRT, coinciding with the first scheduled imaging assessment.

Follow-up sampling: Every 6 months (± 4 weeks) thereafter for up to 24 months from the completion of CCRT, or until disease progression, death, withdrawal of consent, or study completion, whichever occurs first. Additional blood samples may be collected at unscheduled visits if disease recurrence or progression is clinically suspected, to correlate ctDNA status with disease status.

Blood samples will be processed according to a standardized protocol to ensure consistency and minimize preanalytical variability. Specifically, blood samples must be maintained at room temperature and processed within 2 hours of collection to prevent cell lysis and release of genomic DNA that could dilute ctDNA signals. Samples will be centrifuged at 1,600 × g for 10 minutes at 4 °C to separate plasma from cellular components. The plasma supernatant will be carefully transferred to a new tube without disturbing the buffy coat layer and will be subjected to a second centrifugation at 16,000 × g for 10 minutes at 4 °C to remove any residual cells and debris. The resulting cell-free plasma will be aliquoted into 1-mL cryovials, labeled with unique identifiers, and stored immediately at –80 °C until batch analysis. All samples will be tracked using a laboratory information management system to ensure chain of custody and prevent sample mix-ups.

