Secondary outcome include: (1) Overall survival (OS), defined as the time from the initiation of CCRT to death from any cause, with patients who are alive at the time of analysis censored at the date they were last known to be alive; (2) Objective response rate (ORR), defined as the proportion of patients achieving CR or PR at the first imaging assessment (3 months post-CCRT) according to RECIST version 1.1 criteria; (3) Dynamic changes in plasma HPV ctDNA levels expressed as continuous variables (copies per mL) and categorical variables (detectable versus undetectable) at predefined time points (T0, T1, T2, T3, and follow-up time points) during and after CCRT, including assessment of ctDNA clearance kinetics (time to first undetectable ctDNA), nadir ctDNA levels, and patterns of ctDNA dynamics (rapid clearance, slow clearance, persistent detection, or reappearance after initial clearance); (4) Predictive performance of HPV ctDNA for disease recurrence, including calculation of sensitivity (proportion of patients with recurrence who have detectable ctDNA), specificity (proportion of patients without recurrence who have undetectable ctDNA), positive predictive value (PPV; probability of recurrence given detectable ctDNA), negative predictive value (NPV; probability of no recurrence given undetectable ctDNA), and area under the receiver operating characteristic curve (AUC-ROC) for ctDNA as a predictive biomarker, with 95% confidence intervals (CIs); and (5) Concordance between HPV ctDNA status and imaging-based assessment (MRI and/or PET-CT) in detecting residual disease at 3 months post-CCRT and early relapse during follow-up, assessed using Cohen’s kappa statistic and contingency table analysis. Additionally, we will explore the lead time advantage of ctDNA detection, defined as the time interval between ctDNA-detected recurrence and imaging-detected recurrence in patients who experience disease progression (20). The detailed schedule of assessments follows the SPIRIT framework and is presented in **Table 1**, which outlines all study procedures, evaluations, and time points from screening through close-out.

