### Sample size calculation

The sample size was calculated based on the primary endpoint of 2-year progression-free survival (PFS), comparing patients with detectable versus undetectable plasma HPV ctDNA at 3 months after completion of CCRT (T3). Institutional historical data indicate a 2-year PFS of approximately 75% in the ctDNA-negative group, while published studies suggest a rate of approximately 50% in the ctDNA-positive group (21). Based on prior studies of HPV-associated malignancies, we conservatively estimated that 30% of patients would be ctDNA-positive at the T3 assessment. Sample size was estimated using the log-rank test for comparing survival curves between two groups: 
$\text{n}={\left({\text{Z}}_{1}-\alpha {/}_{2}+{\text{Z}}_{1}-\beta \right)}^{2}/\left[{\left(\ln\text{HR}\right)}^{2}\times \text{p}\left(1-\text{P}\right)\right]$.

where 
$Z_{1-\alpha /2}=1.96$ for a two-sided α = 0.05, 
$Z_{1-\beta }=0.842$ for 80% power, and *p* = 0.30 represents the proportion of patients expected to be ctDNA-positive. The hazard ratio (HR) was derived from the assumed survival probabilities (
$S_{\text{ctDNA}+}=0.50$, 
$S_{\text{ctDNA}-}=0.75$), yielding an estimated HR of 2.41. Using these assumptions, a minimum of 48 evaluable patients is required to achieve 80% power to detect a difference in 2-year PFS at a two-sided significance level of 0.05. Allowing for an anticipated 15% attrition rate, the total target enrollment is 57 patients. This sample size is considered feasible for recruitment at a single high-volume tertiary cancer center over the planned 2-year enrollment period and is supported by effect sizes reported in prior studies of ctDNA as a prognostic biomarker in HPV-associated cancers (21, 22).

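### The withdrawal criteria let a consenting patient be taken out of the study, not just off treatment, when toxicity, declining performance status or an SAE stops CCRT, so follow-up can be lost needlessly and perhaps informatively

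*Protocol article*

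**What the plan says.** The Withdrawal criteria open with "Participants may be withdrawn from the study under the following circumstances". Two of the listed circumstances concern treatment and not the patient's willingness to take part: "inability to complete the planned treatment regimen due to unacceptable toxicity or deteriorating performance status" and "occurrence of severe adverse events (SAEs) requiring permanent discontinuation of CCRT". Withdrawal of consent is a separate item, so these two grounds apply to patients who still consent. For those withdrawn, the section says: "Data collected from withdrawn participants up to the point of withdrawal will be included in the analysis". It labels this intention-to-treat and makes no provision for observation afterwards.

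Two other sections bear on the rule. Study design and patients states that "this study does not involve investigational drugs or experimental interventions". Blood sampling and time points for ctDNA detection continues follow-up samples for up to 24 months "or until disease progression, death, withdrawal of consent, or study completion, whichever occurs first".

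**The concern.** In a trial of a drug, stopping treatment and leaving the study are often confused, and the confusion costs outcome data. Here there is even less reason to link them, because CCRT is standard care and the study only observes. A patient who stops CCRT can still give blood, be imaged and be followed for survival.

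The patients exposed to the rule are unlikely to be a random sample. Deteriorating performance status and incomplete curative treatment are plausibly related to progression and death. If such patients leave the study when treatment stops, their later events go unseen and they are censored at the last adequate tumor assessment (PFS), the date last known alive (OS) or the last known date (Statistical analysis). That censoring may be informative. No later analysis plan can recover samples or events that were never collected.

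**Working it through.** **1. Who can be withdrawn.** The permission is discretionary: participants may be withdrawn. Because consent withdrawal is its own item, a consenting patient who stops CCRT can be removed at the investigator's choice. Whether she is kept can differ from one patient to the next.

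**2. Two stopping lists side by side.**

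| Event | Ground for study withdrawal (Withdrawal criteria) | Ends follow-up sampling (Blood sampling) |
|---|---|---|
| Consent withdrawn | yes | yes |
| CCRT not completed (toxicity, performance status) | yes | not listed |
| SAE permanently stopping CCRT | yes | not listed |

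The sampling section does not say that it overrides the withdrawal section. For a patient who stops CCRT, the two give different answers.

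**3. What is lost, by endpoint.**
- *OS and PFS.* Both run from the start of CCRT, so a patient who stops in week 3 is already at risk. OS censoring is defined as "patients who are alive at the time of analysis censored at the date they were last known to be alive". That needs vital status only, not a T3 sample or completed treatment.
- *T0 to T2 samples.* T0 and often T1 will already have been taken. Without follow-up they cannot be related to outcome. T2 is timed from completion of all CCRT, including brachytherapy, so it has no defined date for a patient who never completes.
- *T3.* It is timed at 3 months after completion of CCRT. Most patients who do not complete therefore have no defined T3 whatever the withdrawal rule says. The exception is partial stopping: a patient who stops cisplatin, for instance after grade 4 hematologic toxicity (one of the section's own examples), but finishes radiotherapy and brachytherapy could reach T3 and be classified. The rule allows her to be removed first.

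**4. What the attrition allowance covers.** The Sample size calculation says: "Allowing for an anticipated 15% attrition rate, the total target enrollment is 57 patients". This reproduces: 48 / (1 − 0.15) = 56.5, rounded up to 57. It replaces numbers. It does not make those who remain representative of those who left.

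**5. Whole-cohort event risk, by assumption only.** The plan's inputs (30% ctDNA-positive; 2-year PFS 50% and 75%) imply a 2-year event risk of 0.30 × 0.50 + 0.70 × 0.25 = 0.325. Suppose a fraction *w* of the cohort is withdrawn early and has true 2-year event risk *q*, while those retained have 0.325. The true cohort risk is *w* × *q* + (1 − *w*) × 0.325. Both *w* and *q* are assumed; neither is in the document.

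| *w* | *q* = 0.50 | *q* = 0.70 |
|---|---|---|
| 5% | 0.334 (understated by 0.9 points) | 0.344 (1.9 points) |
| 10% | 0.342 (1.8 points) | 0.362 (3.8 points) |
| 15% | 0.351 (2.6 points) | 0.381 (5.6 points) |

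If the withdrawn patients had the same risk as the rest (*q* = 0.325), there would be no understatement. The table shows what the rule could do under these assumptions, not what it will do.

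**The case against.** The strongest reply is that the primary comparison already depends on completing CCRT. T3 is counted from completion, eligibility requires a patient who is medically able to complete treatment, and the sample size is stated in evaluable patients. A patient who never completes is outside the T3 comparison because of the schedule, not the withdrawal clause. This stands, and it limits the point.

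For the same reason, a reader might infer that the rule biases the planned T3 hazard ratio of 2.41 by some amount in some direction. The documents do not support that. They give no discontinuation rate and nothing on how withdrawals would divide between would-be ctDNA-positive and ctDNA-negative patients. Selective loss of progressors from the first group would lower the ratio, loss from the second would raise it, and balanced loss would leave it about where it was. Nor would the fix below bring early stoppers into the primary comparison by default, so a shift in that ratio would not measure its benefit.

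Two further objections carry less weight. The clause is only permissive: true, but permission without a safeguard leaves follow-up of consenting patients to case-by-case judgement. And a journal article condenses the full protocol, which might keep such patients in follow-up. It might, but this is not mere silence. The article states specific grounds for leaving the study and states which data are used afterwards. The sampling section shows that continued observation is workable, but it does not settle the conflict.

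Multiple imputation for missing data below 20%, with complete-case sensitivity analyses, is reasonable in itself. It cannot stand in for follow-up that was deliberately ended.

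**Conclusion.** The point holds as a poorly fixed rule that should be changed. The text permits study withdrawal of consenting patients because standard treatment stopped, in a study that tests no treatment, and it conflicts with the sampling section. The loss is avoidable and may be informative.

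Its reach is whole-cohort PFS and OS, the usefulness of samples taken at T0 to T2, later ctDNA samples, and T3 status in the patients who stop only part of CCRT. Any effect on the T3 hazard ratio is unknown in size and direction. On the assumptions shown (5% to 15% withdrawn, with 2-year event risk of 50% to 70%), the retained patients would understate the cohort's 2-year event risk by about 1 to 6 percentage points. If withdrawal is rare or unrelated to prognosis, the effect is negligible. The conclusion that the rule is wrong does not depend on those figures; it rests on the wording and the study's design.

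**What to change.** Amend the Withdrawal criteria along these lines:

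> *Stopping or changing CCRT for toxicity, an SAE or inability to complete treatment ends protocol treatment only. Scheduled sampling and follow-up for PFS and OS continue unless the patient withdraws consent.*

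In addition:
- For patients who stop CCRT early, time the post-treatment samples from the last treatment given.
- Report losses before T3 by reason.
- Include early stoppers who give a post-treatment sample in the T3 comparison as a sensitivity analysis, leaving the primary analysis population unchanged.

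The cost is protocol wording, one added timing rule, and continued follow-up of the patients who stop early, presumably few. Recruitment is planned to begin in January 2027, so the change can be made before the first patient enters.

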### Outcome measures

The primary outcome of this study is progression-free survival (PFS), defined as the time from the date of initiation of CCRT to the date of first documented disease progression (according to RECIST 1.1 criteria on imaging studies or histopathologic confirmation), disease recurrence (appearance of new lesions after achieving CR), or death from any cause, whichever occurs first. Patients who are alive and progression-free at the time of analysis will be censored at the date of their last adequate tumor assessment.

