### Statistical analysis

All statistical analyses will be performed using SPSS v27.0 (IBM Corp., USA) and R v4.3.0 or later. Baseline characteristics will be summarized using descriptive statistics: continuous variables as mean ± SD or median (IQR) depending on normality, and categorical variables as frequencies and percentages. Group comparisons (ctDNA-positive vs ctDNA-negative) will use Student’s t-test or Mann-Whitney U test for continuous variables, and χ² or Fisher’s exact test for categorical variables.

Longitudinal ctDNA changes will be analyzed using generalized estimating equations (GEE) or linear mixed-effects models to account for repeated measures, adjusted for baseline covariates such as FIGO stage, tumor size, and nodal status. PFS and OS will be estimated by Kaplan-Meier method and compared with log-rank tests; hazard ratios (HRs) with 95% CIs will be obtained from univariate and multivariate Cox proportional hazards models. Covariates in multivariate models will be checked for collinearity (VIF >5) and proportional hazards assumption (Schoenfeld residuals).

Predictive performance of ctDNA for recurrence will be evaluated using ROC curves (AUC, sensitivity, specificity, PPV, NPV); optimal cut-offs for continuous ctDNA will be determined via Youden’s index. Concordance between ctDNA and imaging will be assessed with Cohen’s kappa. Missing data<20% will be handled by multiple imputation (MICE), with sensitivity analyses including complete-case analyses. Patients lost to follow-up will be censored at the last known date. Two-sided p-values<0.05 indicate statistical significance, with multiple testing correction applied for secondary endpoints. Exploratory subgroup analyses may be conducted by FIGO stage, histology, or baseline HPV type. These subgroup analyses will be exploratory and hypothesis-generating and will not be used for confirmatory subgroup inference.

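### The withdrawal criteria merge stopping treatment with leaving the study, so outcomes can be lost selectively, and two PFS censoring dates apply to patients lost to follow-up

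*Protocol article*

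**What the plan says.** **Leaving the study.** The Withdrawal criteria section opens with "Participants may be withdrawn from the study under the following circumstances". The object is the study, not the treatment. Among the grounds are:
- "inability to complete the planned treatment regimen due to unacceptable toxicity or deteriorating performance status";
- serious adverse events that end CCRT for good;
- non-compliance with follow-up, as the investigator judges it;
- major violations, with the example "failure to obtain required blood samples at critical time points or deviation from prescribed treatment regimens";
- "development of disease progression requiring change in treatment approach during the planned CCRT course".

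**Data kept.** The section closes by stating that "Data collected from withdrawn participants up to the point of withdrawal will be included in the analysis", under the intention-to-treat principle, unless consent to use the data is withdrawn. No collection of progression or vital status after withdrawal is stated.

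**Censoring.** In Outcome measures, patients alive and progression-free "will be censored at the date of their last adequate tumor assessment" for PFS. OS has its own rule there: the date last known alive. Statistical analysis then adds, without naming an endpoint: "Patients lost to follow-up will be censored at the last known date".

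**Setting.** The study tests no drug or other intervention (Study design and patients). The primary comparison groups patients by ctDNA status at T3 (Sample size calculation).

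**The concern.** In an observational cohort, being unable to finish cisplatin or missing a blood draw is no reason to stop recording progression and death. Several of the listed grounds are plausibly linked to prognosis. If outcome data stop at those points, the patients who disappear are not a random sample of the cohort. Calling this intention-to-treat adds to the problem, because that principle requires follow-up whatever happens to treatment.

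The consequence depends on when the patient leaves:
- **Before T3:** she has no T3 ctDNA result. In the primary comparison she is excluded or imputed, which is a selection problem.
- **After T3:** she has a ctDNA group and is censored, possibly for a reason related to her coming event.
- **At any time:** whole-cohort PFS and OS, both timed from the start of CCRT, are exposed to potentially informative censoring.

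The second matter is simpler. A progression-free patient lost to follow-up has two possible PFS times, depending on which section the analyst follows. The later date counts time without tumour assessment as progression-free.

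**Working it through.** **1. The plan's own figure.** Inputs from Sample size calculation: 2-year PFS 0.75 (ctDNA-negative) and 0.50 (ctDNA-positive), 30% positive, two-sided α 0.05, power 80%, attrition 15%.
- HR = ln(0.50)/ln(0.75) = 2.41, as stated.
- (1.96 + 0.842)² / [(ln 2.41)² × 0.3 × 0.7] = 48.3, against the stated 48.
- 48/0.85 = 56.5, rounded up to 57, as stated.

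The figures reproduce. This formula yields a number of events, which the plan reads as patients; that is a separate matter and is not used here. The allowance of 57 − 48 = 9 patients replaces lost numbers. It does nothing about loss related to prognosis.

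**2. Scale of the event count.** Two-year event fraction = 0.3 × 0.50 + 0.7 × 0.25 = 0.325.
- 57 enrolled: 57 × 0.325 = 18.5 events.
- 48 evaluable: 48 × 0.325 = 15.6 events.

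Suppose 3 to 4 events go unrecorded among the patients who leave (an assumption). Those patients belong to the 57, so the base is 18.5: 3/18.5 = 16% and 4/18.5 = 22%.

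**3. Effect of loss after T3 (illustration).** Assume constant hazards, and that a share w of would-be events in a group is censored just before it occurs. The observed hazard in that group is then (1 − w) times the true one. If only T3-positive patients are affected, the apparent HR is 2.41 × (1 − w) and their apparent 2-year PFS is 0.50^(1 − w). Expected events are given for 48 evaluable patients.

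| w (assumed) | Apparent HR | Apparent 2-year PFS, T3-positive | Expected events |
|---|---|---|---|
| 0 | 2.41 | 50% | 15.6 |
| 10% | 2.17 | 54% | 14.9 |
| 20% | 1.93 | 57% | 14.2 |
| 30% | 1.69 | 62% | 13.4 |
| 50% | 1.20 | 71% | 12.0 |

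If the same share is lost in both groups, the HR stays at 2.41 but PFS is overstated in both: at w = 20%, 0.50^0.8 = 57% and 0.75^0.8 = 79%. If only T3-negative patients are affected, the HR moves the other way: at 20%, 2.41/0.8 = 3.01.

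**4. The two censoring dates.** Table 1 and Clinical evaluation and imaging schedule no response assessment between baseline and 3 months after CCRT, and 6-monthly imaging thereafter for the first 2 years.

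| Progression-free patient lost | Rule in Outcome measures | Rule in Statistical analysis |
|---|---|---|
| during CCRT | baseline imaging, so about time zero | last contact |
| between follow-up scans | last scan | last contact, up to about 6 months later |

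**The case against.** **Progression during CCRT.** A reader might infer that these patients are censored for PFS. The documents do not support that. Outcome measures counts first documented progression as an event, and data up to withdrawal are kept. She would be censored only if the progression were clinical and lacked RECIST or histological documentation. What is lost is her OS follow-up.

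**Discretion.** Withdrawal is permitted, not required, and a missed sample appears only as an example of a major violation. This stands against reading the section as an automatic exit. It does not remove the problem: who leaves then depends on individual judgement, with the same loss of data.

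**No express bar on follow-up.** The section says which data are analysed; it does not forbid collecting more. The sampling section names withdrawal of consent, not investigator withdrawal, among the events that end sampling. This is fair. Still, an analysis limited to data up to withdrawal would not use later outcomes even if they were collected.

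**Imputation.** Withdrawing a patient for a missed sample might be read as contradicting the plan to impute missing data. It is only an inconsistency: the two can coexist, but the same missing T3 value may be an exit for one patient and an imputed value for another.

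**Censoring.** The PFS and OS rules are specific, and the general sentence could be read as giving way to them. That is a reasonable reading, but the text does not say so. Since OS already has its own rule, the general sentence has no evident role unless it also covers PFS.

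**Conclusion.** The point holds as a drafting defect with real consequences if the text is followed. Study withdrawal is allowed on prognostic grounds, analysis stops at withdrawal, and this is labelled intention-to-treat. The result is possible selection in the T3 comparison from early exits, and possible informative censoring from later exits and in whole-cohort PFS and OS.

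The size of the bias cannot be derived, because no withdrawal rate by cause is given. The 16–22% figure rests on an assumed 3 to 4 lost events and on the plan's PFS rates applying to all 57 patients. Dividing by the 15.6 events expected in 48 evaluable patients would give up to 26%, but that base already excludes the patients who leave. A reader might also conclude that the HR is biased in a known direction. It is not: the direction depends on which ctDNA group loses more events, and the HR values above are illustrations.

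The censoring ambiguity is a smaller, separate point. It affects only progression-free patients lost to follow-up; 6 months is roughly the maximum gap between follow-up scans, not a typical one. Both points should be corrected before recruitment, planned from January 2027.

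**What to change.** - State that stopping CCRT or missing a blood sample does not end study participation. This concerns data collection only and leaves treatment decisions untouched.
- Keep following every patient who has not withdrawn consent for progression and vital status, and analyse those data. This also restores OS follow-up after progression during CCRT and makes the intention-to-treat wording accurate.
- Record a missed sample as a missing value, handled under the existing missing-data plan.
- Limit censoring at the last known date to OS, and make the last adequate tumour assessment the single PFS censoring rule, including for patients lost to follow-up.

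The cost is protocol wording, plus record or telephone follow-up of a few patients. Long-term clinical follow-up is already planned (Feasibility and limitation).
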